#### Management of Eliminated Cases

The researcher must fill in the elimination reason in the CRF and the CRF should be reserved for future reference. The random number of eliminated cases cannot be replaced.

#### Full Termination Criteria

The experiment should be terminated due to any of the following reasons: there are serious safety issues with the experimental device; the experimental device has a poor effect and there is no need to continue the test; there are major mistakes in the protocol; and there are funding or management problems of sponsor.

### Treatment and Intervention

For all the enrolled patients, stent retriever thrombectomy is the first-line approach. Skyflow device is for the trial group and solitaire FR for control group. Patients who are eligible for intravenous thrombolysis according to the guidelines were given 0.9 mg/kg alteplase. General or local anesthesia was chosen based on the patients' clinical condition and heparin was used selectively. Stent retriever thrombectomy can be performed repeatedly and generally no less than 3 times before rescue therapy. If the intracranial occluded blood vessel had significant stenosis or other lesions after mechanical thrombectomy with stent retriever, the researcher should evaluate whether to perform the aspiration thrombectomy, balloon dilatation, stent implantation or other rescue therapy based on the subject's clinical conditions. If adjuvant rescue treatment was performed, DSA should be recorded and mTICI classification should be reevaluated. Follow-up examinations and visits were carried out according to the test procedure.

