## Abstract

**Background:** Stent retriever thrombectomy is the standard treatment for acute ischemic stroke (AIS) with large vessel occlusion (LVO) in anterior circulation. The aim of the trial is to evaluate whether the new thrombectomy device-Skyflow can achieve the same safety and efficacy as Solitaire FR in the treatment.

**Method:** This study is a prospective, multicenter, stratified randomized, single blind, paralleled, positive controlled, non-inferiority clinical trial. The safety and efficacy of vascular recanalization in AIS patients who are treated with either a new thrombectomy device-Skyflow or with Solitaire FR and within 8 h of symptom onset will be compared. A total of 192 patients will be enrolled, each group with 96 patients. The primary endpoint is successful recanalization rate after the operation. The secondary efficacy endpoints are the time from artery puncture to successful recanalization (mTICI 2b-3), NIHSS scores of 24 h (18–36 h), and 7 ± 2 days after the operation, mRS scores, and the rate of patients with mRS 0–2 scores 90 ± 14 days after the operation, and the success rate of instrument operation. The safety endpoints are the rate of symptomatic intracranial hemorrhage (sICH) and subarachnoid hemorrhage at 24 h (18–36 h) post-operation, incidence of adverse events (AE) and serious adverse events (SAE), all-cause mortality, and incidence of device defects.

**Discussion:** This trial will provide information on the safety and efficacy of Sky-flow stent retriever in the treatment of AIS patients with anterior circulation LVO. The success of this trial will be the basis for the product to be finally officially listed and applied in China.

**Trial registration:** Registered on 11 March 2018 with Chinese clinical trial registry. Registration number is ChiCTR1800015166.

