### Management of Concomitant Medication

Drugs and treatments for underlying diseases, comorbidities or adverse events are permitted. But devices with similar effects to the experimental device or the control device are prohibited for all subjects during clinical trials. If the subject used other drugs and treatments for various reasons during the study period, the investigator needed to record this case in details in the original medical record for future reference and evaluate the possible bias in clinical trial results.

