### Endpoint Measurement

The primary endpoint is successful recanalization rate. It is defined as the proportion of target vessels achieving successful recanalization [modified Thrombolysis in Cerebral Infarction (mTICI) 2b-3].

The secondary efficacy endpoints are the times from artery puncture to successful recanalization (mTICI 2b-3), NIHSS scores 7 ± 2days after the operation, mRS scores and the rate of patients with 0–2 scores 90 ± 14 days after the operation, and the success rate of instrument operation (the rate of instruments being successfully delivered, released, and withdrawn in this group).

The safety endpoints are the rate of symptomatic intracranial hemorrhage (sICH) and subarachnoid hemorrhage at 24 h (18–36 h) post-operation, incidence of adverse events (AE) and serious adverse events (SAE), all-cause mortality and device defects.

sICH is defined as any ICH associated with neurological deterioration assessed by 4 or more points increase on the NIHSS score within 18–36 h. Adverse events are unfavorable medical events that occur during clinical trials, whether related to the test device or not, including hematoma or hemorrhage at the site of puncture, air embolism, infection, distal embolization, vascular spasm, thrombosis, vascular dissection and perforation, embolism, acute occlusion, ischemia, intracranial hemorrhage, pseudoaneurysm formation, neurological deficits including stroke, and death, and device deformation, fracture and malfunction. Serious adverse events are defined as any events which can cause deaths or serious health deterioration that occur during clinical trials, including fatal diseases or injuries, permanent defects of body structure or function, events that need hospitalization or can prolonged hospitalization, events that need medical or surgical intervention in order to avoid permanent defects in body structure or function, and events that can cause fetal distress, fetal death, or congenital anomalies and congenital defects. Device defects refer to the unreasonable risks of medical devices under normal use that may endanger human health and life safety during the clinical trials, such as incorrect identification and device breakage.

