### Reduction and Avoidance of Bias

The following measures have been taken to reduce and avoid bias:

NIHSS and mRS score were assessed by physician independent of the operator in each clinical trial center. The images are reviewed by the core laboratory to assess time of successful recanalization and the grade of the blood flow of the target vessel before and after the operation. When the result is different from the clinician's judgment, the core laboratory result shall prevail.

Sponsors, clinical trial supervisors, and researchers took corresponding measures to reduce the bias on results during the trial, including training for investigators before the start of the study to make sure they are familiar with research procedure and device operation, selecting skilled and experienced surgeons who has completed more than 30 mechanical thrombectomy operations, ensuring that the experimental protocol is strictly followed, following the requirements of relevant treatment guidelines, and data verification after the completion of clinical trials.

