### Sample Size

The calculation of the sample size is based on the successful recanalization rate evaluated during the operation. Based on the results of the North American Solitaire post-marketing study (18), the meta-analysis of thrombectomy devices (2), and a multi-center registered clinical trial (EAST) led by [name] of Tiantan Hospital, it is expected that the test group can reach the same efficiency when the sponsor and clinicians assumed the rate of successful recanalization after treatment was about 90% in the control group. Eventually, a total of 192 patients were enrolled according to calculation based on statistical principles, 96 cases in each group with a 12.5% non-inferiority margin, a 5% significance level (two-tailed), an 80% statistical power and a 5% dropout rate.

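### The primary endpoint does not say whether mTICI 2b-3 is graded before or after rescue, so a vessel opened by rescue can count as a success of the assigned retriever

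*Protocol article*

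**What the plan says.** All references are to the protocol article.

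- **Endpoint Measurement** defines the primary endpoint: "It is defined as the proportion of target vessels achieving successful recanalization [modified Thrombolysis in Cerebral Infarction (mTICI) 2b-3". It gives no time point relative to rescue and does not require that the assigned retriever achieved the result.
- **Abstract**: "The primary endpoint is successful recanalization rate after the operation".
- **Sample Size**: "The calculation of the sample size is based on the successful recanalization rate evaluated during the operation".
- **Treatment and Intervention** makes stent-retriever thrombectomy first line: "Stent retriever thrombectomy can be performed repeatedly and generally no less than 3 times before rescue therapy". If significant stenosis or another lesion remains, "the researcher should evaluate whether to perform the aspiration thrombectomy, balloon dilatation, stent implantation or other rescue therapy based on the subject's clinical conditions". Then: "If adjuvant rescue treatment was performed, DSA should be recorded and mTICI classification should be reevaluated".
- **Reduction and Avoidance of Bias** has the core laboratory, whose result prevails over the clinician's, assess "the grade of the blood flow of the target vessel before and after the operation". No separate pre-rescue grade is named.
- **Management of Concomitant Medication**: "devices with similar effects to the experimental device or the control device are prohibited for all subjects during clinical trials".
- **Statistical Analysis** compares the primary endpoint in the full analysis and per-protocol sets, and requires the lower 95% limit of the difference to exceed −12.5 points. It gives no rule for rescued patients.

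**The concern.** The objective is to evaluate one device against another for registration. For that question the informative outcome is what the assigned retriever achieved. If the deciding grade is taken after rescue, a retriever failure later opened by aspiration, balloon or stent is scored as a success of the retriever.

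The arm with more device failures has more failures for rescue to convert, so with comparable rescue the two rates move towards each other. In a superiority trial that costs power. In a non-inferiority trial it favours the claim. The article's Discussion itself expects Skyflow to grip and cut thrombus less strongly than Solitaire FR, so an excess of device-only failures in the test arm is a risk that the article raises itself.

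The Discussion also states that researchers cannot be blinded, and the decision to use rescue is theirs. Independent reading of the images does not remove the problem, because rescue changes the vessel that is read.

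**Working it through.** **1. The plan's own sample size.** Inputs from Sample Size: 90% in both arms, margin 12.5 points, two-sided 5%, power 80%, dropout 5%.

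n = (1.96 + 0.8416)² × 2 × 0.9 × 0.1 / 0.125² = 90.4, so 91 per arm. 91 / 0.95 = 95.8, so 96 per arm and 192 in total. The stated size reproduces.

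**2. What a post-rescue grade does to the difference.** Let p be the device-only success rate and s the share of all device failures that rescue turns into mTICI 2b-3 (the proportion rescued times the success rate among those rescued). Then:

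final rate = p + (1 − p)s

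If s is the same in both arms, final difference = (1 − s) × device-only difference.

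**3. Illustration.** The article gives no rescue rate and no device-only rate, so these are assumptions: device-only success 80% (control) and 67.5% (test), a deficit exactly at the margin. The chance of declaring non-inferiority is the probability that the lower 95% Wald limit exceeds −12.5 points, by exact binomial enumeration with 96 per arm and no stratification.

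| s | Control final | Test final | Deficit (points) | Chance of declaring non-inferiority |
|---|---|---|---|---|
| 0 (pre-rescue grade) | 80% | 67.5% | 12.5 | 2.6% |
| 0.25 | 85% | 75.6% | 9.4 | 8% |
| 0.30 | 86% | 77.25% | 8.75 | 10% |
| 0.50 | 90% | 83.75% | 6.25 | 26% |
| 0.70 | 94% | 90.25% | 3.75 | 63% |

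For example, s = 0.25 arises if half of the failures are rescued and half of those are opened (0.5 × 0.5). Of these rows, only s = 0.50 brings the control rate to the 90% that the plan assumes. A normal approximation with 91 per arm gives similar values: 2.5%, 7.7% and 24.0% at s = 0, 0.25 and 0.50.

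**4. Unequal rescue success.** With the same device-only rates:

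- 50% of control and 25% of test failures opened: 90% against 75.6%, and the deficit widens to 14.4 points.
- 25% of control and 50% of test failures opened: 85% against 83.75%, and the deficit falls to 1.25 points.
- Break-even with control at 50%: 0.675 + 0.325s = 0.90 − 0.125, so s = 0.10 / 0.325 = 0.31. Below about 31% in the test arm the deficit no longer shrinks.

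**5. Power if the pre-rescue grade is primary.** With equal arms and 91 evaluable per arm, power = Φ(0.125 / √(2p(1 − p)/91) − 1.96).

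| Device-only rate | Power at 91 per arm | Total size for 80% power, 5% dropout |
|---|---|---|
| 90% | 80% | 192 |
| 85% | 66% | 272 |
| 80% | 56% | 340 |

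**The case against.** **No sentence says that the re-scored grade is the primary one.** This stands. A second grading implies that a first one exists, and Sample Size speaks of evaluation during the operation. A reader might infer a fixed rule that rescue successes are credited to the device. The text supports only that this is allowed and is the more natural reading.

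**The core laboratory may read more than two time points.** This also stands. The article does not limit it to a before and an after grade, and the same sentence has it assess when recanalization was reached.

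**The bias need not favour Skyflow.** Correct. Shrinkage needs roughly similar rescue success, and discretionary rescue by unblinded operators does not guarantee that. An endpoint that can move in either direction with operator choice is still a poor basis for a device comparison.

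**The size is assumed.** Correct. Rescue is linked to residual stenosis or other lesions and left to judgement, so not every failure would be rescued. This favours the smaller values of s.

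**Rescue and the per-protocol set.** Because devices with similar effects are prohibited, a reader might infer that a rescued patient leaves the per-protocol set. The article does not say so. Elimination Criteria lists only false enrolment and use of neither study device, and the concomitant-treatment section asks that other treatments be recorded and their possible bias evaluated. The prohibition may also be aimed at other stent retrievers; aspiration is the debatable case.

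**A condensed article may leave this to the full protocol.** This does not carry far. The article defines the endpoint, describes rescue and orders a re-score, and the wording it chooses leans towards the post-rescue grade.

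**Conclusion.** The point holds as an undefined primary endpoint. The article does not state which mTICI grade decides the trial. Its end-of-procedure wording and the re-score after rescue favour the post-rescue grade, and nothing prevents a rescued vessel from counting as a success of the assigned retriever. For a device non-inferiority claim, the pre-rescue grade answers the question better.

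On the post-rescue reading, with similar rescue success in both arms, a deficit at the margin would pass with a probability of about 8% to 26% when rescue opens 25% to 50% of failures, against 2.6% on the pre-rescue grade. These figures rest on the assumed rates of 80% and 67.5% and on unstratified Wald limits. They show the mechanism and do not estimate this trial's error rate. The documents do not support a stated rule crediting rescue to the device, a bias of certain direction, or removal of rescued patients from the per-protocol set.

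**What to change.** 1. Define the primary endpoint as core-laboratory mTICI 2b-3 after the last pass of the assigned retriever and before any rescue device. Score a vessel that needed rescue to reach 2b-3 as a failure, in both the full analysis and per-protocol sets.
2. Report the final post-rescue mTICI grade as a secondary endpoint.
3. Confirm whether the 90% planning rate refers to this definition. If it does not, restate the power or the sample size.
4. Reconcile Treatment and Intervention, which allows aspiration and other rescue, with Management of Concomitant Medication, which prohibits devices with similar effects. No clinical rule is proposed here, and the scoring change affects no patient's treatment.

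The cost is revised endpoint wording and one more graded time point. The pre-rescue angiographic run must be available to the core laboratory; the article explicitly asks for a DSA record when rescue was performed but does not name a pre-rescue run. The main downside is lower stated power if the device-only rate is below 90%: 66% at 85% and 56% at 80%, with 91 evaluable per arm.

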### Management of Concomitant Medication

Drugs and treatments for underlying diseases, comorbidities or adverse events are permitted. But devices with similar effects to the experimental device or the control device are prohibited for all subjects during clinical trials. If the subject used other drugs and treatments for various reasons during the study period, the investigator needed to record this case in details in the original medical record for future reference and evaluate the possible bias in clinical trial results.

### Endpoint Measurement

The primary endpoint is successful recanalization rate. It is defined as the proportion of target vessels achieving successful recanalization [modified Thrombolysis in Cerebral Infarction (mTICI) 2b-3].

The secondary efficacy endpoints are the times from artery puncture to successful recanalization (mTICI 2b-3), NIHSS scores 7 ± 2days after the operation, mRS scores and the rate of patients with 0–2 scores 90 ± 14 days after the operation, and the success rate of instrument operation (the rate of instruments being successfully delivered, released, and withdrawn in this group).

The safety endpoints are the rate of symptomatic intracranial hemorrhage (sICH) and subarachnoid hemorrhage at 24 h (18–36 h) post-operation, incidence of adverse events (AE) and serious adverse events (SAE), all-cause mortality and device defects.

sICH is defined as any ICH associated with neurological deterioration assessed by 4 or more points increase on the NIHSS score within 18–36 h. Adverse events are unfavorable medical events that occur during clinical trials, whether related to the test device or not, including hematoma or hemorrhage at the site of puncture, air embolism, infection, distal embolization, vascular spasm, thrombosis, vascular dissection and perforation, embolism, acute occlusion, ischemia, intracranial hemorrhage, pseudoaneurysm formation, neurological deficits including stroke, and death, and device deformation, fracture and malfunction. Serious adverse events are defined as any events which can cause deaths or serious health deterioration that occur during clinical trials, including fatal diseases or injuries, permanent defects of body structure or function, events that need hospitalization or can prolonged hospitalization, events that need medical or surgical intervention in order to avoid permanent defects in body structure or function, and events that can cause fetal distress, fetal death, or congenital anomalies and congenital defects. Device defects refer to the unreasonable risks of medical devices under normal use that may endanger human health and life safety during the clinical trials, such as incorrect identification and device breakage.

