### Statistical Analysis

For descriptive analysis, enumeration data will be expressed by frequency and composition ratio, and the measurement data will be expressed by the mean, standard deviation, maximum, minimum, median, 25th and 75th quantile.

For baseline demographics, all date will be analyzed based on full analysis set. Continuous calibration Chi-square tests or Fisher's exact tests will be used for comparison of enumeration data between groups. Group *t-*test will be used for comparison of normally distributed measurement data between groups, and Wilcoxon Rank Sum test for non-normally distributed measurement data.

For the primary outcome, the successful recanalization rate of blood vessels, the CMH chi-square analysis with adjusted center effect will be used for comparison between groups based on full analysis set and per protocol set. In addition to the success rate, the difference in the success rate between the experimental group and the control group and the 95% confidence interval with the lower bound greater than −12.5% will be also estimated.

Other efficacy indicators comparation between groups will be the same as the baseline analysis. The paired *t-*test will be used for the intra-group comparison of normally distributed measurement data and the Wilcoxon Sign Rank test for the intra-group comparison of non-normally distributed measurement data.

For safety evaluation, the number and proportion will be used to describe cases that were normal before treatment and abnormal after treatment in the full analysis set. Adverse events will be described by number and incidence, and this incidence will be tested by continuous calibration Chi-square tests or Fisher's exact tests. At the same time, the specific manifestations and extent of all adverse events in each group and their relationship with the research products will be described in detail.

For missing data, only the missing primary endpoint indicators will be carried forward during analysis, while other indicators will be not. Incorrect and unreasonable data will be checked by the electronic data capture (Electronic Data Capture, EDC) system and the question will be answered by the researcher before statistical analysis. For patients withdrawing from the trial, the information will still be included in the final statistical analysis.

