All data will be analyzed using SAS9.4 software and all statistical analysis will be performed at the two-sided 0.05 significance level (except for special instructions).

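### The sICH definition has no death criterion and no reference NIHSS, and a non-significant difference test with 96 patients per arm cannot support a claim of equal safety

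*Protocol article*

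**What the plan says.** Endpoint Measurement in the protocol article defines sICH as "any ICH associated with neurological deterioration assessed by 4 or more points increase on the NIHSS score within 18–36 h". The endpoint itself is "the rate of symptomatic intracranial hemorrhage (sICH) and subarachnoid hemorrhage at 24 h (18–36 h) post-operation". Neither sentence mentions death or names the NIHSS from which the rise is counted.

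Table 1 schedules NIHSS before the operation, at Visit 3 (24 h, window 18–36 h) and at 7 ± 2 days. Post-operative brain CT or MR is scheduled at Visit 3 only.

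The other safety endpoints are "incidence of adverse events (AE) and serious adverse events (SAE), all-cause mortality and device defects". The list of adverse events, which carries no time window, includes "intracranial hemorrhage, pseudoaneurysm formation, neurological deficits including stroke, and death".

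On analysis, the Abstract asks whether the new device "can achieve the same safety and efficacy as Solitaire FR in the treatment". The Statistical Analysis section gives the primary endpoint a confidence-interval criterion (lower bound above −12.5%). For safety the only inference it states concerns adverse events: "this incidence will be tested by continuous calibration Chi-square tests or" Fisher's exact tests, under the general rule that "all statistical analysis will be performed at the two-sided 0.05 significance level". For missing data, only the primary endpoint is carried forward; other indicators are not.

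**The concern.** There are two linked problems.

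1. **Who is counted.** The rule needs an NIHSS value obtained at 18–36 h. A patient who bleeds and dies earlier has none and fails the definition, and no other stated rule brings the patient back. The omission affects the most severe cases of the safety endpoint listed first. Because the reference NIHSS is not named, sites could also classify the same survivor differently.
2. **What the comparison can show.** Efficacy has a margin and an interval; the safety inference stated in the article is a test for a difference. In a trial sized for recanalization, such a test will usually be non-significant even if bleeding is materially more frequent in one arm. The trial is meant to support product registration, so a safety statement that leaned on that result would not be supported by the data.

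**Working it through.** **Plan's own figure.** Inputs from Sample Size: 90% recanalization in both arms, margin 12.5%, two-sided 5%, power 80%, dropout 5%.

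n = (1.960 + 0.842)² × 2 × 0.90 × 0.10 / 0.125² = 90.4, so 91 per arm. Then 91 / 0.95 = 95.8, so 96 per arm and 192 in total. This reproduces the stated number. Safety does not enter the calculation.

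**Definition, case by case.**

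| Patient | NIHSS at 18–36 h | Counted as sICH? | Counted elsewhere? |
|---|---|---|---|
| ICH, alive at Visit 3, at least 4 points worse than before the procedure | yes | yes, if the window is the assessment time and the reference is the pre-procedure score | AE/SAE |
| ICH at about 6 h, worse then, no further worsening during 18–36 h | yes | depends on the reading: yes if the window is when NIHSS is assessed, no if it is when the worsening must occur | AE/SAE |
| ICH, dies before 18 h | none | no, on either reading | death, AE, SAE |

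**Power of the stated difference test if applied to sICH.** The document gives no sICH rate, so the control rate p is an assumption, ranged over 2–10%. Power is the sum of Bin(a; 96, 2p) × Bin(b; 96, p) over all pairs of event counts (a, b) for which the two-sided test gives p < 0.05.

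| Control vs doubled rate | Corrected chi-square | Fisher's exact | Uncorrected chi-square |
|---|---|---|---|
| 2% vs 4% | 4.0% | 4.0% | 11.1% |
| 3% vs 6% | 8.1% | 8.5% | 14.8% |
| 4% vs 8% | 12.1% | 13.4% | 20.1% |
| 5% vs 10% | 16.3% | 18.1% | 25.8% |
| 6% vs 12% | 21.2% | 22.4% | 31.1% |
| 8% vs 16% | 32.1% | 32.2% | 40.6% |
| 10% vs 20% | 42.4% | 42.5% | 49.8% |

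With the corrected test a true doubling is thus non-significant in about 58–96% of trials. With 91 evaluable per arm its power is 4–40%.

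**How much is due to the correction.** At an assumed 6% in both arms the corrected test rejects in 2.0% of trials and the uncorrected test in about 4.5%, so the correction is conservative. But the uncorrected test still misses a doubling from 6% in 69% of trials. For 80% power, even without correction, 1141 per arm would be needed for 2% vs 4%, 435 for 5% vs 10%, and 199 for 10% vs 20%. The sample size is the main cause.

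**What an interval would show.** Take 10/96 against 5/96, a doubled rate. The difference is +5.2 points, with a Newcombe (score-based) 95% interval of −2.7 to +13.5 and a corrected chi-square p = 0.28. The p-value is unremarkable; the interval shows that a large excess has not been excluded. With 5 control events, 15 events in the test arm, a threefold rate, are needed before p falls below 0.05.

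Approximate half-width with equal rates of 6%: 1.96 × √(2 × 0.06 × 0.94 / 96) = 0.067, or ±6.7 points.

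**The case against.** The strongest reply is that early fatal bleeds are not lost to the trial. All-cause mortality, AEs and SAEs are safety endpoints in their own right, and intracranial hemorrhage and death are listed as AEs without a time window. All AEs must be recorded, and withdrawn patients' information stays in the final analysis. This stands: the loss is from the sICH rate only. It does not remove the defect, because mortality mixes bleeding with every other cause of death and the sICH rate is the endpoint that isolates it.

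Other points that stand:

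- The window can be read as the time of assessment, so a survivor who deteriorated early and is still worse at Visit 3 would count. The death before Visit 3 is missed on either reading.
- The test is stated for AE incidence; sICH is not named. Applying it to sICH is an inference, a reasonable one since intracranial hemorrhage is a listed AE. Fisher's exact test is the stated alternative and performs almost the same.
- Low power for safety endpoints is ordinary in a trial sized on efficacy, and the continuity correction is a minor contributor.
- The article condenses a fuller protocol, so the absence of a safety interval from it is not in itself a fault. The point is that the inference it does state cannot carry the aim it states.

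Stronger readings are tempting. A reader might infer that the sponsor will read a non-significant safety test as proof of equal safety. No section says so, and the Objective speaks only of evaluating safety and efficacy. A reader might also infer that patients who die early leave the sICH denominator. The missing-data rule says only that non-primary values are not carried forward, not that such patients are removed. Nor does the document give any number of deaths before 18 h, so the size of the undercount cannot be stated.

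**Conclusion.** The point holds in two limited parts.

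First, the sICH rule as written excludes a patient who dies of an intracranial bleed before Visit 3 and leaves the reference NIHSS open. This follows from the definition and Table 1 and needs no numerical assumption. Its effect on the rate cannot be quantified from the document.

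Second, a non-significant difference test cannot support the equal-safety aim in the Abstract. If the stated test is applied to sICH with 96 per arm, a doubled rate is detected with about 4–42% power (11–50% uncorrected). This rests on assumed control rates of 2–10% and on extending the AE test to sICH. The conclusion is the same over the whole range and for all three tests, and it comes mainly from sizing the trial on recanalization.

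The correction should be made, but the point does not touch the primary endpoint, and it does not show that harm would go unrecorded.

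**What to change.** **Definition.** Define sICH as any ICH from the procedure through 36 h with a rise of 4 or more NIHSS points from the pre-procedure baseline, or with death, whether or not Visit 3 took place. Keep all treated patients in the denominator.

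**Analysis.** Report sICH, subarachnoid hemorrhage, SAEs and death as risk differences with two-sided 95% score intervals. State that equal safety will not be concluded from a non-significant p-value. If a formal claim of comparable safety is wanted, the sponsor would have to set and justify a limit for the interval beforehand; none is given in the document. Dropping the continuity correction is optional and changes little.

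**Cost.** Mostly wording, since deaths and AEs are already recorded. ICH in patients who die before Visit 3 must be confirmed from unscheduled imaging or AE records, because Table 1 schedules no earlier post-operative scan. The sICH rate may rise slightly. The intervals will be wide, about ±6.7 points at an assumed 6%, so the safety statement will be more cautious.
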